**● Safety Evaluation (Phase II)**

In calculating the target number of participants for the safety evaluation cohort, with the expected value of 20% for hypoxemia (<90%), threshold at 40%, significance level of 0.05 on both sides and statistical power of 80%, required number is 43 cases. In consideration of drop-out, we set the target at 45 cases.

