Frequency of apnea (≥20 sec), degree of patients’ satisfaction and coordination during procedure will be evaluated with capnography group and nasal pressure monitor group, and the difference between those two groups will be analyzed using Pearson’s chi-square test. Significance level will be 0.05 on both sides, and confidence interval, and **two-sided 95% confidence interval will be computed.**

- - 1. **Safety Analysis**

Frequency of adverse event occurrence is the evaluation items to consider safety, therefore data table will be created. To estimate the proportion, exact 95% confidence interval for binomial distribution will computed for each group. Inter-group comparison will be carried out as required using Fisher's exact test.

- - 1. **Intermediate Analysis**

Data will be locked when registration of all cases for the Safety Evaluation (Phase II) is completed. The fixed analysis results will be disclosed to the independent data-monitoring committee (IDMC) (see 11.6) that oversees the study. The IDMC will evaluate the fixed data, and when they find the following situation, the study will be discontinued without carrying out registration for the usefulness evaluation.

- Rate of discontinued cases due to default accounted for 20% or more.
- Hypoxemia (SpO_2_<90%) was found in 60% or more of the cases.
- The IDMC determined that it will be inappropriate to conduct usefulness evaluation.

When the IDMC verified the safety, the participants will be registered for the usefulness evaluation. No intermediate analysis will be carried out in the usefulness evaluation.

- 1. **Independent Data-Monitoring Committee (IDMC)**

The independent data-monitoring committee (IDMC) will be established for this study. The IDMC will be independent of the people who conduct the study, and consist of two or more specialists whose position have no conflict of interest with this particular clinical study. The IDMC will provide appropriate advice and guidance in order to secure the safety of the participants and ethical and scientific soundness, based on the data monitoring protocol that is determined elsewhere for the purpose of securing safety of the participants. In cases where serious adverse events appear in this clinical study, the principal investigator may request the IDMC to deliberate concerning whether or not the study should be continued or revision of the Study Protocol. The IDMC will serve in writing the results of the deliberation to the principal investigator.

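### The Phase II requirement of 43 cases for 80% power rests on a normal approximation; binomial power at 43 is 77.1%, and the claim is met at the full target of 45

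*Protocol*

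**What the plan says.** Protocol section 11.2, Safety Evaluation (Phase II), gives all the inputs. The two rates are stated as "expected value of 20% for hypoxemia (<90%), threshold at 40"%. The level, the power and the resulting number follow: "significance level of 0.05 on both sides and statistical power of 80%, required number is 43 cases. In consideration of drop-out, we set the target". The number then set is 45, two more than required. So 43 is offered as the evaluable number that secures 80% power, and the other two as a reserve.

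The section names neither the formula nor the test that will compare the observed rate with 40%. Elsewhere the protocol gives one method for a single proportion, in 11.5.3 (Safety Analysis): "To estimate the proportion, exact 95% confidence interval for binomial distribution will computed for each group". That sentence concerns adverse-event frequency and is not assigned to the Phase II hypoxemia comparison.

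**The concern.** In a single-arm test of a proportion the event count is a whole number, so the test cannot use its full 5%, and power moves in a saw-tooth as the sample size changes. A normal-approximation sample size ignores this. With about 40 patients, one event more or less in the rejection limit shifts power by roughly 8 to 10 points. The approximation can therefore name a sample size at which the real test falls short of the stated power.

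If that happens at 43, the protocol prints a power that its own required number does not have, and the two extra patients are not a true reserve. With no test named, there would also be room to read 11 events in 43 patients as excluding 40% when the stated level does not allow it.

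**Working it through.** **Inputs, all from 11.2:** null rate p0 = 0.40, alternative p1 = 0.20, two-sided level 0.05, power 0.80, required number 43, target 45.

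**1. Reproduce the plan's figure.** The one-sample normal approximation with null and alternative variances is

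n = [(z0.975·√(p0(1−p0)) + z0.80·√(p1(1−p1))) / (p0−p1)]²

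= [(1.960·√0.24 + 0.8416·√0.16) / 0.20]² = [(0.9602 + 0.3366) / 0.20]² = 42.04, rounded up to 43.

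This matches the protocol. The same approximation puts power at 43 at 81.0%.

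**2. Find the rejection limit at n = 43.** Here X is the number of patients with hypoxemia.

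| Test | 10 events | 11 events |
|---|---|---|
| Equal-tailed exact, lower tail (reject at ≤0.025) | 0.0162 | 0.0354 |
| Minimum-likelihood exact, two-sided p (reject at ≤0.05) | 0.0285 | 0.0614 |
| Mid-p, lower tail (reject at ≤0.025) | 0.0114 | 0.0258 |
| Score z with null variance (reject at ≤−1.96) | −2.24 | −1.93 |
| Wald z (reject at ≤−1.96) | −2.60 | −2.17 |

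Two of these by hand:
- Mid-p at 11: 0.0162 + ½(0.0354 − 0.0162) = 0.0258.
- Score at 11: (11/43 − 0.40)/√(0.24/43) = −0.1442/0.0747 = −1.93.

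The first four tests reject at 10 and not at 11. Only Wald rejects at 11.

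**3. Power at n = 43.**
- Limit 10: P(X ≤ 10 | 43, 0.20) = 0.7711, which is 80.0 − 77.1 = 2.9 points below the claim.
- Limit 11 (Wald): P(X ≤ 11 | 43, 0.20) = 0.8645, with lower-tail error P(X ≤ 11 | 43, 0.40) = 0.0354 instead of 0.025.

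The score test uses the same null variance as the formula in step 1. So 43 falls short even under the test that belongs to that formula.

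**4. Effect of the drop-out allowance.**

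| Evaluable n | Test | Limit | Lower-tail error | Power at 20% |
|---|---|---|---|---|
| 45 | Equal-tailed exact, minimum-likelihood, mid-p, score | 11 | 0.0216 | 82.6% |
| 44 | Equal-tailed exact | 10 | 0.0124 | 74.6% |
| 44 | Minimum-likelihood, mid-p, score | 11 | 0.0277 | 84.6% |
| 43 | Equal-tailed exact, minimum-likelihood, mid-p, score | 10 | 0.0162 | 77.1% |

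At 44 with 11 events the minimum-likelihood two-sided p is 0.0455, the mid-p lower tail is 0.0201 and the score z is −2.03, so all three reject. The equal-tailed exact test does not, because 0.0277 exceeds 0.025. The total two-sided size at 44 is 0.0455 for the minimum-likelihood test and 0.064 for the score test.

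Losing both reserve patients therefore takes power from 82.6% to 77.1% under all four tests.

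**The case against.** The case against is substantial.

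- **The formula is conventional and correctly applied.** This stands: 43 reproduces exactly. What does not hold is the power printed next to it.
- **The full target meets the claim.** This also stands. With 45 evaluable patients, power is 82.6%. Assessment is one sedated procedure plus some hours of monitoring, so losses may well be few.
- **No decision in the protocol uses this test.** The Phase II criteria in 11.5.4 rest on discontinuations of 20% or more, hypoxemia in 60% or more, or the committee's judgement. None of them involves a comparison with 40%. This stands and limits the practical consequence. The 3.5% error from accepting 11 of 43 is a risk of leaving the test open, not a rule that the protocol contains.
- **The test may be named in the SAP, which is not shown.** True, but the power claim is printed in the protocol, and of the five tests checked only Wald brings 43 above 80%.

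A reader might infer that losing even one patient takes power below 80%. The document does not support that. The 74.6% at 44 holds only for the equal-tailed exact test, while a minimum-likelihood exact test, which is also a valid two-sided 0.05 test, has 84.6%. Nor can the equal-tailed test be taken as prescribed because 11.5.3 asks for an exact interval: that instruction is written for adverse-event tables.

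**Conclusion.** The concern holds in a limited form. At the evaluable number that 11.2 calls required, power is 77.1% and not 80%, and this is the same for the equal-tailed exact, minimum-likelihood exact, mid-p and score tests. The stated power is reached with all 45 evaluable. It is lost if both reserve patients drop out, and with 44 it depends on a test that 11.2 does not name.

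The result rests on the protocol's own 20%, 40% and two-sided 0.05, and on independent binary outcomes. The shortfall is 2.9 points, enrolment is adequate if nobody is lost, and the go/no-go rule does not depend on it. This is a minor correction to a statement that is wrong as printed.

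**What to change.** In 11.2, name the test that compares the Phase II hypoxemia rate with 40%, restate power by exact binomial calculation for that test, and delete the statement that 43 cases give 80% power. If the equal-tailed exact test is chosen, the text could read:

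*With 45 evaluable patients the equal-tailed exact binomial test has 82.6% power at a true rate of 20%; 40% is rejected at 11 or fewer cases. With 43 evaluable the limit is 10 and power is 77.1%.*

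A figure for 44 should be added only once the test is fixed, since it is 74.6% or 84.6% depending on that choice.

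The cost is a sentence or two of text and no change in enrolment. The downside is a slightly less favourable stated power if patients drop out.

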**● Usefulness Evaluation (Phase III)**

The purpose of the usefulness evaluation is to prove that there is no difference in the incidence rate of hypoxemia (SpO2 <90%) between nasal pressure monitor group and capnography group, meaning that nasal pressure monitor is not inferior to capnography. According to reports, the incidence rate of declined SpO_2_ to under 90% in the endoscopic procedure under sedation is 12–47% when propofol is used as sedative,[4, 8, 9, 10] With regard to required number of registered patients, calculation based on 20% hypoxemia incidence rate, with non-inferiority margin of 15% for nasal pressure monitor against capnography, statistical power of 80% and significance level of 0.05 on both sides results in 224 patients for both groups (112 patients respectively).

- 1. **Handling Case Records**

In principle, the principal investigator and statistic specialists will decide on how the information on cases will be handled. In principle, the principal investigator and a statistic specialist will decide on how the information on cases will be handled.

- 1. **Handling Data**

When computing or analyzing data, as a rule, the data will be handled as shown below. If a question arises, it will be resolved through discussion between a statistic specialist and the study coordinator.

Missing data will not be supplemented. As sensitivity analysis, mixed-effects model for repeated measures, which compensates for data mission, will be used. Details will be contained in the Statistical Analysis Plan.

- 1. **Statistical Analysis Items and Plan**

● Safety Evaluation (Phase II)

Carry out analysis after the data is fixed following the completion of study involving all cases that are the subjects of safety evaluation. In the usefulness evaluation of all participants, the primary analysis will be the analysis of the FAS, and analysis of the PPS that complies with the Study Protocol will be carried out as a reference. Safety analysis will be carried out with the SAS.

Details of the statistical analysis will be determined in the Statistical Analysis Plan, which will be prepared elsewhere before the data is locked.

● Usefulness Evaluation (Phase III)

Data from the usefulness evaluation will be analyzed after it is fixed following the completion of the study that involves all cases. In the usefulness evaluation of all participants, the primary analysis will be the analysis of the FAS, and analysis of the PPS that complies with the Study Protocol will be carried out as a reference. Safety analysis will be carried out with the SAS.

Details of the statistical analysis will be determined in the Statistical Analysis Plan, which will be prepared elsewhere before the data is locked.

- - 1. **Patient Background Analysis**

Patient data distribution and summary statistics will be obtained for each group by population. With regard to nominal variables, frequency of the category and proportion will be shown for each group. With regard to metric variables, summary statistics (number of cases, mean value, standard deviation, minimum value, median and maximum value) will be obtained for each group. In the comparison between two groups, Pearson's chi-square test will be used for nominal variables, but if the cells with expected frequency <5 account for 20% or more, Fisher’s exact test will be used. The t-test will be used for metric variables. Significance level will be 0.05 on both sides.

- - 1. **Usefulness Analysis**
       1. **Primary Analysis**

The main purpose of the study is to verify using the incidence rate of hypoxemia as primary endpoint that nasal pressure monitor is not inferior to capnography. Frequency and proportion in each group will be collated and **two-sided 95% confidence interval will be computed** When the upper limit of the 95% confidence interval in the comparison of hypoxemia incidence rate goes 15% lower than the non-inferiority margin, we deem that non-inferiority was proven.

To verify the null hypothesis that incidence rate of hypoxemia in both groups is the same in the primary analysis, Mantel–Haenszel test will be applied to the data stratified using assignment factors. Significance level will be 0.05 on both sides.

- - - 1. **Secondary Analysis**

Secondary analysis regarding usefulness will be carried out for the purpose of giving supplementary consideration to the results of primary analysis. No multiplicity adjustment will be carried out in the secondary endpoints analysis regarding usefulness .

Frequency of apnea (≥20 sec), degree of patients’ satisfaction and coordination during procedure will be evaluated with capnography group and nasal pressure monitor group, and the difference between those two groups will be analyzed using Pearson’s chi-square test. Significance level will be 0.05 on both sides, and confidence interval, and **two-sided 95% confidence interval will be computed.**

- - 1. **Safety Analysis**

Frequency of adverse event occurrence is the evaluation items to consider safety, therefore data table will be created. To estimate the proportion, exact 95% confidence interval for binomial distribution will computed for each group. Inter-group comparison will be carried out as required using Fisher's exact test.

- - 1. **Intermediate Analysis**

Data will be locked when registration of all cases for the Safety Evaluation (Phase II) is completed. The fixed analysis results will be disclosed to the independent data-monitoring committee (IDMC) (see 11.6) that oversees the study. The IDMC will evaluate the fixed data, and when they find the following situation, the study will be discontinued without carrying out registration for the usefulness evaluation.

- Rate of discontinued cases due to default accounted for 20% or more.
- Hypoxemia (SpO_2_<90%) was found in 60% or more of the cases.
- The IDMC determined that it will be inappropriate to conduct usefulness evaluation.

When the IDMC verified the safety, the participants will be registered for the usefulness evaluation. No intermediate analysis will be carried out in the usefulness evaluation.

- 1. **Independent Data-Monitoring Committee (IDMC)**

The independent data-monitoring committee (IDMC) will be established for this study. The IDMC will be independent of the people who conduct the study, and consist of two or more specialists whose position have no conflict of interest with this particular clinical study. The IDMC will provide appropriate advice and guidance in order to secure the safety of the participants and ethical and scientific soundness, based on the data monitoring protocol that is determined elsewhere for the purpose of securing safety of the participants. In cases where serious adverse events appear in this clinical study, the principal investigator may request the IDMC to deliberate concerning whether or not the study should be continued or revision of the Study Protocol. The IDMC will serve in writing the results of the deliberation to the principal investigator.

If the principal investigator determines in light of such results that it immediately requires emergency response due to urgency and influence of the situation, registration can be temporarily stopped, notification can be sent to related personnel and other similar measures can be taken.

- 1. **Final Analysis**

After the completion of follow-up period, case data will be fixed and analysis will be carried out. Analysis officer will prepare the Analysis Report and submit it to the study coordinator and the principal investigator.

1. **Compliance with Study Protocol and Nonconformity Management**
2. The principal investigator and assistant investigators will adhere to the Study Protocol and conduct the clinical study in order to avoid urgent risk for the participants, unless there are inevitable medical reasons.
3. Nonconformity in accordance with the Clinical Trials Act means incompliance with regulations, study protocol, manual, etc. and falsification and fabrication of research data. Deviation from the Study Protocol is also included in nonconformity.
4. The principal investigator or assistant investigators will record all nonconformities regardless of the reason.
5. When the principal investigator finds nonconformity, he/she will report it to the manager of the participating institution. When assistant investigators find nonconformity, they will promptly report it to the principal investigator. However, if it is a minor deviation that is acceptable based on the Study Protocol, the principal investigator and assistant investigators will decide the need for reporting to the manager of the participating institution.
6. When the principal investigator finds an especially serious nonconformity, he/she will promptly report to the Approved Clinical Study Review Board. Measures to prevent recurrence of such situation will be taken and assistant investigators will be informed of such situation. Serious nonconformity under such situation means those events that influence the human rights and safety of the participants of the study, progress of the study and its confidence, for example, serious breach of eligibility/exclusion criteria or discontinuation rules.
7. **Changes regarding Study Protocol, Case Report or Analysis Plan**
   1. **Revising Study Protocol and Case Report**
8. The person who oversees the study, when it is deemed necessary, will provide a proposal to revise the Study Protocol or case report to the principal investigator together with latest annexed document and other necessary reference materials and information.
9. The research administrator will give sufficient consideration to the materials and information mentioned in the previous paragraph that he/she provides to the principal investigator, and allow adequate time for the principal investigator to consider the matters.
10. The principal investigator will promptly submit the revised Study Protocol or case report to the head of the participating institution and promptly acquire approval of the Approved Clinical Study Review Board
11. If it is determined that changes have to be made to the Study Protocol that was submitted to the Minister of Health, Labour and Welfare, a notification regarding such changes will be submitted.
    1. **Revising Analysis Plan**

When the content of the Analysis Plan is revised, the statistics specialist will enter all changes in the Analysis Report for the study. A record will be kept of all such changes to the Analysis Plan.

1. **Cancellation, Discontinuation or Completion of the Study**
   1. **Standard for Canceling or Discontinuing the Study**

If the information described in the following paragraphs is revealed and it is thought that continuing with the study may be difficult, the research administrator will discuss whether to cancel or discontinue the study with the principal investigator and decide on the appropriate course of action.

1. Appearance of unexpected serious adverse events.
2. Information suggesting that it will be impossible to forecast the tendency for expected serious adverse events to occur, including the number of cases or the incidence rate and the conditions under which they appear, based on the results of the questionnaire and the package insert.
3. Cases where information is revealed which shows that some of the serious adverse events, which were previously thought to have no causal relationship, actually have an undeniable causal relationship in light of the occurrence tendency revealed in the data, such as number of cases, the frequency, and the conditions under which they occur.
4. Study reports showing that the testing equipment defect occurrence tendency, including the number of cases, frequency and the conditions under which the defect occurs, has significantly changed.
5. Study reports showing that there is a risk of causing cancer or other serious illnesses, disorders, or death.
6. Information suggesting that the trial in question will not prove the usefulness of the testing equipment.
7. Information showing that the equipment has no benefit or effect on the illness that is the subject of the study.
8. In cases where information is acquired regarding measures that the authorities will take to prevent the occurrence of a health hazard and its spread, such as stopping the manufacture, importation or sale of medical devices that contain parts used in the testing equipment, collecting such devices, and/or disposing of them.
9. In cases where after the completion of the safety evaluation the IDMC determines that it is inappropriate to continue with the study.
   1. **Procedure to Cancel or Discontinue the Study**

In cases where the study will be cancelled or discontinued after discussion among the study investigators, the principal investigator will promptly inform the head of the participating institution in writing regarding the details and the reasons involved. The principal investigator will also inform eligible participants of the same, and take appropriate measures, such as changing treatments to a more appropriate type.

- 1. **Procedure for Cancelling or Discontinuing the Study at the Individual Institution**

In cases where the study is cancelled or discontinued, the principal investigator will promptly inform the head of the participating institution in writing regarding the details and the reasons involved.

- 1. **Completion of the Study**

After the completion of the study, the principal investigator will notify the head of the participating institution in writing regarding the fact that the study has been completed, and provide documents showing a summary of the results of the study.

1. **Data Management**
   1. **Data Entry Method and Management**
2. Submitting Case Report Forms (CRFs).

Submit all CRFs to the data center.

1. Enter all CRFs into the system.

The data center will use a system, with which it is possible to acquire access logs and validation, to enter the CRF data and create data sets.

1. Keep CRFs.

The original CRFs will be kept at the data center.

1. Database Lock

The database will be locked after it has been verified by the principal investigator.

- 1. **Identification of First-hand Entry into CRFs (Raw Data)**

In this clinical study, the following documents will be deemed original data (raw data).

1. Records concerning the consent of the participants and information provided to the participants.
2. Records that form the basis for CRFs, such as medical records, nursing records, clinical examination data, and scan images. Data stored in electronic medical records is also deemed raw data.
3. Monitoring records that were recorded in the testing equipment and then transferred to a hard drive.
4. Records concerning the use of testing equipment.
5. Documents or records that are essential to the study in light of the guiding principle of the clinical study.

The items shown below are, when entered in CRFs, regarded as raw data. However, when they are contained in medical records, such medical records are regarded as raw data.

1. The aim of concomitant drugs or therapy.
2. The degree of adverse events, the outcome (including the results at the time of follow-up examination), the severity, decisions regarding the causal relationship with this particular testing equipment, and the reasons for such decisions.
3. The reasons for participant dropout.
4. The comments of the principal investigator or assistant investigators.
5. **Storing Raw Data and Other Records**

Information concerning participants that is recorded in the monitor (CSM-1901) will be transferred using USB and stored in a hard drive. The hard drive, consent forms and CRFs will be securely kept under the supervision of the principal investigator.

The head of the research institution and the principal investigator must appropriately store essential documents regarding the research, etc. (including copies of application forms, notifications from the head of hospital, copies of various applications/reports, the participant identification code list, consent forms, copies of case reports and other documents/records that are required to guarantee the credibility of the data) until at least five (5) years have passed from the date on which the study was completed.

The locked data will also be appropriately managed at the Division of Biostatistics of Keio University Hospital Clinical and Translational Research Center.

1. **Direct Perusal of Raw Data**

The head of the participating institution and the principal investigator will guarantee that investigators from monitoring organizations, the audit committee, the Approved Clinical Study Review Board, or government authorities are able to see all records, including raw data. They will verify that the study is conducted appropriately and that the credibility of the data is sufficiently secured.

1. **Quality Control and Assurance in the Study**
   1. **Quality Control**

The study will be audited for the purpose of verifying that it is conducted in accordance with the Study Protocol and that data is accurately collected and stored. Audits will be carried out in accordance with the Guidelines regarding Clinical Study Monitoring and Audits. In the main audit, the data entered in the CRFs that is accumulated in the data center will be regularly monitored. Such processes will follow the auditing procedure determined elsewhere to manage quality control at the institution (onsite/offsite monitoring) according to the degree of risk involved.
Personnel involved in audits must report the result of such audits/monitoring to the principal investigator. They must not leak information that has been acquired through their involvement in the work without due reason, even after ceasing to be involved in the work.

- 1. **Quality Assurance**

No audit will be conducted to assure the quality of the clinical study.

1. **Ethics**

This clinical study will be carried out in compliance with the Clinical Trials Act and the Declaration of Helsinki.

1. **Confidentiality**

The principal investigator must verify that personal information of participants is kept confidential.

1. In CRFs, participants are identified only with a unique identification code.
2. Documents containing the personal information of the participants, such as consent forms, will be handled by assistant investigators as confidential documents.
3. **Approved Clinical Study Review Board**

Prior to the commencement of this clinical study, the Authorized Clinical Study Review Board of the participating institution will examine the ethical, scientific and medical appropriateness of the study. The clinical study will be conducted after obtaining the approval of the Approved Clinical Study Review Board. The Authorized Clinical Study Review Board will continue to review the performance of the study at least once a year.

1. **Expected Advantages/Disadvantages Arising from the Study**
   1. **Expected Advantages**

Among the testing equipment used in the clinical study, capnography has been approved for use in the treatments used in this clinical study and has also been listed for use under National Health Insurance. It has been used in normal clinical practice. Although the nasal pressure monitor has yet to be approved as a medical device, the ability to constantly measure and provide early detection of respiratory abnormalities has proven to be useful, meaning that it can bring benefits to clinical practice. However, as the cost of drugs and treatments during the study period is paid for by the participants with contributions from private insurance and national insurance, patients gain no medical or economical advantage over normal medical treatment by participating in the study.

- 1. **Expected Disadvantages**

As mentioned above, although the nasal pressure monitor has yet been to be approved, nocturnal polysomnography, which applies the same principle, is widely used in normal medical practice. As seen in 6.2. Important Findings regarding the Testing Equipment, there are no disadvantages for patients, however, eligible participants (see 3.) will be carefully considered in order to minimize risk. Furthermore, consideration will also be given to the method of study (see 5.) as shown below. ① Sedatives will be administered by an endoscopist who has been fully trained in sedation by an anesthesiologist. ② The strength of the sedatives during the procedure will be controlled between BIS 60 and 80 as shown on the monitor. ③ In cases where SpO_2_ is observed to have declined (<90), apnea lasts for ≥20 seconds, or a respiratory abnormality (≤8 bpm or abnormal waveform) accompanied by a decline in SpO_2_ (<95%) is observed during sedation, the doctor in change of sedation will report the respiratory abnormality to the endoscopy team, and measures will be taken to improve respiration.

In cases where a serious or unexpected adverse event appears, the principal investigator may, as required, request the deliberation of the IDMC. Such adverse events will be carefully considered and investigated in accordance with the Clinical Trials Act and other relevant regulation, and necessary measures will be taken.

1. **Compensation for Health Damage and Insurance**
   1. **Compensation for Health Damage**

With regard to health damage, the principal investigator etc., will endeavor to assist in the recovery of the patient in question and offer appropriate medical treatment. The cost of treating such health damage will be handled in accordance with the cost contribution arrangement of the patient in the specified clinical study, etc.

- 1. **Enrollment in Clinical Trial Insurance (Compensation Insurance)**

The principal investigator and assistant investigators will enroll in a clinical trial insurance (compensation insurance) in order to be able to perform their responsibilities in cases where it is necessary to deal with health damage.

- 1. **Enrollment in Liability Insurance**

In addition to compensation insurance, the principal investigator and assistant investigators will enroll in liability insurance.

1. **Monetary Payments**

Costs for patients will not increase by participating in the study. Examination, treatment and other procedures relating to the primary condition and other complications will be provided within the scope of the coverage provided under National Health Insurance.

1. **Conflicts of Interest and Research Funds**

This clinical study will be conducted with funding from the Treatment Section of the Department of Gastroenterology and/or the hospital. No funds or benefits, etc., will be provided by Nihon Kohden Corporation, which is the manufacturer and retailer of the testing equipment, and researchers will plan and conduct the study independent of the company. The testing equipment will be loaned from Nihon Kohden Corporation at no cost.

This research (study) will be fairly conducted by the chief researcher (principal investigator) and assistant researchers (assistant investigators) of Chiba University. Research funds will be managed based on the Fund Plan. In terms of conflicts of interest in relation to this study, all interests will be appropriately managed in accordance with the Policy regarding Conflicts of Interest Associated with Clinical Studies after obtaining the approval of the Conflict of Interest Committee of Chiba University Hospital. The transparency of the study with regard to conflicts of interest will be maintained through regular reporting of the course of the research (trial) to the Conflict of Interest Committee. There are no conflicts of interest that should be disclosed to the principal investigator and assistant investigators for this clinical study. [name] of the Department of Anesthesiology, Pain and Palliative Care Medicine is one of the inventors of the measuring technology which formed the basis for the development of the testing equipment, and the patent for such technology is held by Nihon Kohden Corporation and Chiba University (Respiratory Status Screening Device: Patent Application No. 6204086 and 6075972).

1. **Disclosure of Information regarding the Study**

The principal investigator will enter a summary of the study in the Clinical Trial Study Protocol/Research Outline Disclosure System (http://jrct.niph.go.jp/) prior to the commencement of the study, and update the Study Protocol as required based on the revision and progress of the study. Documents to be disclosed will be the Study Protocol, the Audit Plan, the Statistical Analysis Plan, and the General Report. When the clinical study is completed, the results of the study will be entered without delay.

1. **Announcement of Results**
   1. **Announcement Method**

The principal investigator will announce the results of the study without delay when the study has been completed . When doing so, necessary measures will be taken to protect the human rights, other rights and benefits of researchers and related personnel. Methods of announcement will include presentation at academic conferences, publication in journals, and entry on public databases.

- 1. **Rules for Announcement**

The main thesis for publication will be submitted to an English language journal. Public release of the study without the results of endpoint analysis by the research administrator or the principal investigator by means of presentation at academic meetings or submission as a general article for the purpose of introducing the study, or by announcing patient background distribution or safety data at an academic meeting or by means of submission to a journal after the completion of registration may be carried out after obtaining the approval of the principal investigator. Announcement of other contents that do not include the main analysis and/or final analysis will not be carried out, with the exception of cases in which the approval of the IDMC has been obtained. In principle, the first author who announces the thesis containing the main research results (primary endpoint analysis results) will be decided through discussion, and the final author will be the principal investigator, with co-authors who contributed greatly to the study, based on the restrictions of the journal to which the thesis will be submitted. The principal investigator will decide whether personnel from the research office should be included in the list of authors according to the degree of their contribution. Authors who will release a minor thesis other than the main one (e.g. a report regarding secondary endpoints, a thesis regarding secondary analysis) will be selected by the research administrator. All co-authors will review the content of the thesis before submission and consent to the content. In cases where a co-author candidate does not agree with the content even after discussion, the research administrator may exclude such person from the co-authors.

